## DFEND

The numbers, proportions and reasons for withdrawal from trial will be summarised by treatment arm. The distribution of times between randomisation and withdrawal from follow-up will be summarised using a histogram.

The baseline characteristics of those missing follow-up will be compared to those with complete follow-up. The relationship between baseline characteristics and missing data will be investigated graphically. Missing data patterns will be examined using a logistic predictor of missingness model.

### **2.6 Adverse event reporting**

Adverse events (AE), adverse reactions (AR), serious adverse events (SAE) and serious adverse reactions (SAR) will be summarised by intervention arm and time point.

### **2.7 Assessment of outcome measures (unblinding)**

The outcome assessors, trial statistician and all members of the study team will be blinded. The data monitoring committee (DMC) may be unblinded at their request, and if they are unblinded, will be reminded not to unblind the trial statistician or other members of the study team at the beginning of every meeting.

### **2.8 Descriptive statistics for outcome measures**

Each of the outcome measures will be described by treatment group. Means and standard deviations or medians and interquartile ranges will be used for continuous variables; Q-Q plots will be used to assess whether the distribution of a variable is normal. Frequencies and proportions will be used to describe categorical variables.

### **3. *Data analysis plan – Inferential analysis***

#### **3.1 Main analysis of treatment differences**

The main statistical analyses will estimate the difference in mean outcomes between patients randomised to the vitamin supplementation and placebo by intention to treat at 6 months' post randomisation on the PANSS. ATE estimates will be summarized at 3, 6 months for the primary outcome and at 6 months for secondary outcomes. We will also estimate subpopulation (baseline vitamin D insufficient and sufficient) specific treatment effects for all statistical models.

Missing post randomisation assessments will be dealt with by fitting adequate linear models to all the variables using maximum likelihood methods. Such an approach provides valid inferences under the assumption that the missing data mechanism is ignorable (MAR) and if predictors of missingness are included as covariates in the model.

The significance level will be 5% (two-sided) for specified analyses. Group difference estimates and associated 95% confidence intervals will be reported.

The trial statistician will remain blind until the main analyses have been completed. The analysis of the secondary outcome of vitamin D concentrations at 6 months will be carried out after all other analyses are completed as there is a high expectation that mean concentration will be higher in the intervention group.

Sensitivity analyses will be used to assess the robustness of conclusions to missing outcome data and to departures from randomised treatment.

##### **3.1.1 Analysis of primary outcomes**

###### **Primary Efficacy Parameters**

- A. To determine whether the addition of 120,000 IU monthly of vitamin D supplement to standard treatments is more effective than placebo in improving PANSS total score at six-month follow-up in those with First Episode Psychosis

The main objective of the statistical analyses is to assess the effect of vitamin D supplementation on the primary outcome PANSS total score at the 6-month follow-up time point. To this end linear mixed modelling (LMM) will be employed.

Linear mixed modelling utilises all available information, leading to more precise estimates of the treatment effect at the time points. This technique will allow the simultaneous modelling of the repeated outcome time points, description of the course of the outcomes over time in the two intervention groups and evaluate the resulting differences between the groups.

Prior to modelling the longitudinal effect of the intervention groups over the time course of the study, spaghetti plots will be used to examine patterns of the outcome over time.

The total scores are assumed to arise from a normal distribution. This will be checked and if this is found not to be appropriate, transformations may be used.

In such models the outcome variable measured at the post treatment time points (here 3 and 6 months) features as the dependent variable with, with treatment arm (vitamin D or placebo), time (3 or 6 months), time by treatment arm interaction, baseline PANSS and the randomization stratifier (ethnicity) included as covariates.

In this longitudinal analysis, each participant acts as a cluster. Therefore, for the random part of the model, random intercepts that vary at the participant level will be used.

The Stata command 'mixed' will be used to fit the model. Treatment differences will be estimated for each time point separately using the 'lincom' command, enabling the outcome at the primary endpoint to be found this way.

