## 10.2 Analysis

The primary analyses of efficacy will be based on the intention-to-treat sample, utilising all available follow-up data from all randomised participants. The significance level will be 5% (2-sided) for all specified main and secondary analyses with estimates and confidence intervals presented for all effects.

All descriptive analyses, recruitment rate, consent rate, loss to follow-up, departures from randomised treatment and the prevalence of serious adverse events post-randomisation will be reported and summarised by treatment arm over the course of the study. All causes of withdrawal from randomised treatment will be reported. BMI will be calculated using the following formula:  $\text{weight (kg)}/\text{height (m)}^2$ .

The main objective of the formal statistical analyses is to assess the effect of vitamin D supplementation on the primary outcome PANSS total Score at the 6 month follow-up time point. To this end linear mixed modelling (LMM) will be employed.

In such models the outcome variable measured at the post treatment time points (here 3 and 6 months) features as the dependent variable with, treatment arm (vitamin D or placebo), time (3 or 6 months), baseline PANSS and randomisation stratifier (ethnicity) included as covariates. The model will also contain a subject-varying random intercept to account for any correlation between the repeated measures.

Treatment effects on secondary outcomes will be assessed using similar modelling techniques, employing generalisations to non-normal data where necessary.

We will also estimate subpopulation (baseline vitamin D insufficient and sufficient) specific treatment effects for the primary outcome and secondary outcomes except for 25OHD blood concentration levels by including relevant interaction terms between baseline vitamin D insufficiency status and treatment group in the statistical models.

We expect there to be some missing data in the post-treatment outcomes variables. The LMM analyses are based on maximum likelihood and will provide valid inferences under a missing at random (MAR) missingness mechanism. We will explore predictors of missingness, if deemed suitable for adjustment we will include these as explanatory variables in the analyses. If post

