#### **Stratification and clustering**

Randomisation has been stratified by ethnicity (two level categorical variable; white or other). Therefore, it is important to include this variable in the modelling process. The level of the stratification factor that has the largest number of participants will be used as the reference category in the modelling.

The structure of primary outcome (and some of the secondary outcome) data is longitudinal with repeated measurements. This correlation of observations within participants will be accounted for in the modelling process by including a subject-varying random intercept.

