### Model assumption checks

The models assume normally distributed outcomes; this will have been checked when describing the data and if substantial departures from normality occur, transformations will be considered. Residuals will be plotted to check for normality and inspected for outliers. Bootstrapping of the standard errors (and subsequent confidence intervals) may be considered where residuals appear non-normal.

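### The primary model pools the residual variance of months 3 and 6, so the 6-month standard error is right only if the two visits have equal residual variance, and the plan has no committed safeguard if they do not.

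*Combined protocol and SAP*

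**What the plan says.** SAP 3.1.1 (Analysis of primary outcomes) models PANSS total at 3 and 6 months jointly. The fixed part has treatment arm, time, "time by treatment arm interaction, baseline PANSS and the randomization stratifier (ethnicity) included as covariates". For the covariance, "for the random part of the model, random intercepts that vary at the participant level will be used".

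SAP 3.1.3 (Stratification and clustering) repeats this: "This correlation of observations within participants will be accounted for in the modelling process by including a subject-varying random intercept". Protocol 10.2 agrees: "The model will also contain a subject-varying random intercept to account for any correlation between the repeated measures".

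On fitting, SAP 3.1.1 states: "The Stata command 'mixed' will be used to fit the model". Maximum likelihood is named in SAP 1.9, 3.1 and 3.1.3, and the 6-month contrast is taken with `lincom`. On the test level, SAP 3.1 says: "The significance level will be 5% (two-sided) for specified analyses".

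The nearest safeguard is under Model assumption checks in SAP 3.1.3: "Bootstrapping of the standard errors (and subsequent confidence intervals) may be considered where residuals appear non-normal". Neither document mentions visit-specific residual variances, an unstructured covariance, a baseline-by-time term or robust standard errors.

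**The concern.** A participant random intercept with independent, equal-variance residuals at two visits is the same as compound symmetry with one common variance. The one baseline term also imposes a single baseline slope. Two things can make the real residual variances differ: the spread of PANSS may change between month 3 and month 6, or baseline may predict one visit better than the other. The model then reports a 6-month standard error that mixes in the month-3 variance.

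At stake are the confidence interval and p-value of the sole primary endpoint. If month 6 is the noisier visit, the interval is too narrow and the test exceeds 5%. If month 6 is the quieter visit, the interval is too wide and power is lost. The PANSS subscales are affected in the same way, because SAP 3.1.2 carries the same model over to outcomes measured repeatedly.

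**Working it through.** **Inputs from the documents.** N = 240, 1:1 allocation, 20% attrition at 6 months (192 analysed, 96 per arm), PANSS SD 15.0, two-sided 5% (SAP 1.3, 1.8, 3.1; protocol 10.1).

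**Assumed inputs, not in the documents.** SDs by visit, the correlation of baseline with each visit, the correlation between visits (0.65 or 0.7), and 10% missing at month 3. Baseline SD is set to 15.

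**Step 1: the plan's own figure.** Detectable difference = SD × (z₀.₉₇₅ + z₀.₈₀) × √(4/N), with z₀.₉₇₅ + z₀.₈₀ = 2.8016.
- N = 200: 15 × 2.8016 × √(4/200) = 5.94
- N = 180: 15 × 2.8016 × √(4/180) = 6.26

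The stated 6 to 6.3 units reproduces. The implied standard error is 15 × √(2/96) = 2.165.

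**Step 2: formula for complete data.** Let s₃, s₆ be the visit SDs, r₃, r₆ the correlations with baseline, and s_b the baseline SD. The visit-specific slopes are b₃ = r₃s₃/s_b and b₆ = r₆s₆/s_b, and the common slope is b = (b₃ + b₆)/2. The residual variances after the common slope are

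v₃ = s₃²(1 − r₃²) + (b₃ − b)²s_b², and v₆ likewise.

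Model SE / true SE at month 6 = k = √[(v₃ + v₆)/(2v₆)], and the actual two-sided error is 2[1 − Φ(1.96k)].

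Example, SD 15/15 with correlations 0.6/0.5: b = 0.55; v₃ = 225 × 0.64 + 0.05² × 225 = 144.56; v₆ = 225 × 0.75 + 0.05² × 225 = 169.31; k = √(313.87/338.62) = 0.963; error = 2[1 − Φ(1.887)] = 5.9%.

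| SD m3/m6 | r₃/r₆ | v₃ | v₆ | k | Error |
|---|---|---|---|---|---|
| 15/15 | 0.6/0.6 | 144.00 | 144.00 | 1.000 | 5.0% |
| 15/15 | 0.6/0.55 | 144.14 | 157.08 | 0.979 | 5.5% |
| 15/15 | 0.6/0.5 | 144.56 | 169.31 | 0.963 | 5.9% |
| 15/15 | 0.7/0.5 | 117.00 | 171.00 | 0.918 | 7.2% |
| 13/15 | 0.7/0.5 | 86.83 | 169.39 | 0.870 | 8.8% |
| 15/14 | 0.6/0.5 | 145.00 | 148.00 | 0.995 | 5.1% |
| 15/12 | 0.6/0.5 | 146.25 | 110.25 | 1.079 | 3.5% |

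**Step 3: simulation under the null with dropout.** N = 240, 10% missing at month 3 and 20% at month 6, SAP model fitted by maximum likelihood with z tests.

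- Between-visit correlation 0.65, 3,000 trials per scenario (Monte Carlo SE about 0.4 to 0.5 points): SD 15/15 with 0.6/0.6, 4.4%; 15/15 with 0.6/0.5, 6.2%; 15/15 with 0.7/0.5, 7.6%; 13/15 with 0.7/0.5, 9.3%; 15/12 with 0.6/0.5, 3.4%.
- Between-visit correlation 0.7, 8,000 trials (Monte Carlo SE about 0.25 points): 15/15 with 0.6/0.6, 5.3%; 15/15 with 0.7/0.5, 7.8% (mean model SE 1.69, empirical SE 1.86); 16/14 with 0.65/0.5, 5.6%; 16/13 with 0.6/0.55, 3.5%. A more extreme assumption (13/17 with 0.65/0.45, between-visit correlation 0.65) gave 10.4%.

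The month-6 estimate showed no material bias in these runs, where dropout was unrelated to arm.

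**Step 4: the alternative model.** Unstructured covariance with baseline by time gave 4.3% to 5.5% across both sets. In the 8,000-trial set its 6-month SE was 1.55 to 2.17, at or below about 2.165, the value the sample size already assumes.

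**The case against.** The strongest reply is that a random-intercept model for two follow-up visits is a recognised, prespecified choice, and it is correctly specified if the residual variances are equal. Nothing in the documents says that they differ. This stands: the equal-variance simulations gave 4.4% and 5.3%.

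A reader might infer that baseline must predict month 3 better than month 6, so that the month-6 variance is larger and the test anti-conservative. The documents do not support that. They give no PANSS SD or correlation by visit. Even if the baseline correlation does fall, the residual variance rises only if the total SD does not fall enough to offset it. With correlations 0.6/0.5, a one-point drop in SD at month 6 (15 to 14) brings the error from 5.9% back to 5.1%.

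It can also be said that the SAP plans spaghetti plots and residual plots and allows bootstrapped standard errors. These help little. The bootstrap is optional and triggered by non-normality, and no decision rule is attached to the plots. SAP 3.1.4 covers departures from missing at random and changes to eligibility, not the covariance structure.

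Two related complaints are minor. Using maximum likelihood rather than REML changes the SE by roughly 1% at this sample size. Borrowing from month 3 with a common slope produced no material bias when dropout was unrelated to arm. Only in a deliberately adverse case, with dropout driven by month-3 score in opposite directions by arm, did the SAP model's 6-month contrast shift, by up to 0.5 PANSS units.

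**Conclusion.** The concern holds in conditional form. As specified, the primary test has its nominal level only if the residual variances at months 3 and 6 are equal after a shared baseline slope, and the plan neither justifies that assumption nor commits to a remedy if it fails. The size is about 5% with equal residual variances, about 6% to 9% in the moderate scenarios where month 6 is more variable, and about 3.5% with lost power for SD 15 then 12. Every one of these figures rests on assumed visit SDs and correlations, and the direction cannot be read from the documents.

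It would go too far to conclude that the primary confidence interval and p-value are wrong, or that the test is inflated. The estimand and the treatment-by-time contrast are unaffected, and the point estimate is unaffected when dropout is unrelated to arm. This is a should-fix: an avoidable assumption on the primary test that is cheap to remove.

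**What to change.** Before unblinding, amend SAP 3.1.1 and 3.1.3 and protocol 10.2:

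- Replace the random intercept with an unstructured residual covariance across the two visits, in Stata `mixed ... || id:, noconstant residuals(unstructured, t(visit))`.
- Add baseline PANSS by time; keep treatment by time and ethnicity.
- Apply the same specification to the three PANSS subscales.
- Optional minor refinement: fit by REML with a small-sample degrees-of-freedom method.

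The cost is a wording change, one line of code, one extra variance parameter (two variances and a covariance instead of a common variance and a covariance) and one extra slope. No new data are needed and the sample size of 240 stands. The timing matters because a covariance structure chosen after results are seen would be data-driven.

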### **Planned Subgroup Analysis**

- B. To determine whether the addition of 120,000 IU monthly of vitamin D supplement to standard treatments is more effective than placebo in improving PANSS total score at six-month follow-up in those with First Episode Psychosis who have suboptimal vitamin D concentrations at baseline (defined as less than 50 nmol/L).

To estimate treatment effects in the planned subgroup analyses we will include a treatment x time x baseline vitamin D insufficiency status interaction term (and all lower order interaction terms) as covariates in the modelling process.

As mentioned previously, we will produce estimates of ATE (relating to whole FEP target population) as well as estimates of average treatment effects within the vitamin D deficient (not deficient) subpopulations.

We will also estimate treatment effects in this subgroup (using an interaction term in the models) for all secondary outcomes except for 25OHD blood concentration levels.

### **3.1.2 Analysis of secondary outcomes**

#### **Secondary Efficacy Parameters**

Treatment effects on all secondary outcomes that were measured repeatedly over the follow-up period will lend themselves to the analysis described above. These secondary outcomes will be assessed using similar modelling techniques, employing generalisations to non-normal data where necessary or transformation of the outcome variable. Where secondary outcomes are only measured once over the follow up period, generalised linear models will be used.

1. Positive and Negative Syndrome Scale (PANSS) at 3 months
2. PANSS Positive Scale subscore at 3 and 6 months
3. PANSS Negative Scale subscore at 3 and 6 months
4. PANSS General Psychopathology Scale subscore at 3 and 6 months
5. Global Assessment of Functioning (GAF) at 6 months
6. Calgary Depression Scale (CDS) at 6 months
7. Waist circumference (cm) at 6 months
8. BMI (kg/m^2) at 6 months
9. Total Cholesterol (mmol/L) at 6 months
10. HbA1c (mmol/mol) at 6 months

## DFEND

11. CRP (mg/L) at 6 months
12. Efficacy of vitamin D supplementation at 6 months indicated by 25OHD blood concentration level

### **Safety of Vitamin D**

These analyses are based in the safety data and describe safety outcomes. Chi squared tests (Fisher's Exact test where expected count in any cell is less than 5) will be used to describe any differences. SAEs will be defined in accordance with the EU clinical trial directives. The potential adverse events that we have anticipated we will summarise separately.

AEs will be tabulated by event type and clinical classification by time, phase and randomised group. Each table will detail the number of participants that were still in the trial at the time points by randomisation group. If any adverse events are selected as being of interest they will be further summarised; outlining the severity (mild, moderate, severe) and if classified serious, the expectedness (expected, unexpected) of the event. Any death will be reported as a serious adverse event.

### **Mechanism of action**

The study is based on the theoretical model that vitamin D supplementation might improve psychotic symptoms (PANSS) by increasing blood vitamin D levels to sufficient levels. We wish to investigate this empirically by partitioning any detected vitamin D supplement effect on PANSS into two components: (a) A part that is mediated via changing blood concentration levels (indirect effect) and (b) a non-mediated part (direct effect). To this end we will employ appropriate mediation methods such as the product of coefficients method or linear structural equation models. These methods rely on the assumption that all confounders of the blood level – PANSS path have been measured and included in the models [6].

### **Inflammatory markers**

Exploratory moderator analyses not considered for the primary publication, please see section 3.2.

### **3.1.3 Statistical considerations**

#### **Time points**

This analysis will use data from all available time points. Deviations of measurements from planned time points will be summarised by treatment group.

#### **Stratification and clustering**

Randomisation has been stratified by ethnicity (two level categorical variable; white or other). Therefore, it is important to include this variable in the modelling process. The level of the stratification factor that has the largest number of participants will be used as the reference category in the modelling.

The structure of primary outcome (and some of the secondary outcome) data is longitudinal with repeated measurements. This correlation of observations within participants will be accounted for in the modelling process by including a subject-varying random intercept.

## DFEND

### Missing items in scales and subscales

The number (%) with complete data will be reported. The ideal approach would be to use missing value guidance provided for scales, if provided by the authors. As an alternative, scales will be pro-rated for an individual if 20% or fewer items are missing. For example, in a scale with 10 items, prorating will be applied to individuals with 1 or 2 items missing. The average value for the 8 or 9 complete items will be calculated for that individual and used to replace the missing values. The scale score will be calculated based on the complete values and these replacements.

### Missing baseline data

Missing baseline data should not be an issue for the primary analysis. Some extensions to this analysis may use other baseline variables; if these contain missing data, the number with complete data will be reported and they will be imputed using a method suitable (single round of multiple imputation) to the variable as per the recommendations of White et al [7] .

### Missing outcome data

The mixed model will be fitted using maximum likelihood methods that are valid under the MAR assumption. However, this assumption relates to the variables that are included in the model. To allow for a variable which predicts missingness, this variable needs to be included as either one of the explanatory or dependent variables in the model. Should the investigation into missingness indicate any demographic or clinical baseline variables that are predictors of outcome missingness then such variables will be included as covariates in the model if deemed suitable for adjustment.

If post treatment variables such as compliance with treatment, or baseline variables not suitable to adjust for in the main analyses, are found to be predictive of drop out, multiple imputation will be considered.

### Method for handling multiple comparisons

No adjustment will be considered for multiple comparisons, allowing reviewers to make their own adjustment to estimates if they wish [8].

